### Objectives

#### Primary Objective

The primary objective of the study is to explore phenotypes and estimate the activity degrees of monocytes, NK cells, and CD4^+^ and CD8^+^ T cells (including the CD4/CD8 T ratio) in COVID-19 patients’ peripheral blood. A dominant phenotype of these cell populations in patients affected by severe pneumonia could represent a possible therapeutic target. In fact, severe pneumonia and ARDS seems to follow excessive and disruptive inflammation sustained by monocytes in peripheral blood and macrophages in the lungs. NK cells play a pivotal role in antiviral responses and in regulating the activity of dendritic cells, monocytes, and macrophages, and this makes them extremely intriguing in this study. Simultaneously, cytokines and other soluble factors will be measured in plasma. Differences are expected among COVID-19 patients with varying disease severities and healthy people.

#### Secondary Objectives

The secondary objectives are to identify protective factors, using anamnestic data, such as preceding vaccinations, comorbidities, clinical presentation of COVID-19 in terms of clinical signs and symptoms, and biochemical findings. The recognition of a population of patients safe from excessive inflammation against SARS-CoV-2 could define a risk score for the severity of COVID-19, which could allow for the best clinical choice tailored to each patient. Moreover, favorable immunological pattern identification could be followed by implementation of prophylactic or therapeutic immunomodulatory treatments.

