### Recruitment

The proposed study aims to analyze patients with confirmed SARS-CoV-2 infection by real-time reverse transcription polymerase chain reaction (RT-PCR) assays on throat swabs in order to identify differences in their immune responses. Patients will be recruited at the Emergency Department of “Ospedale di Circolo – ASST Sette Laghi,” University of Insubria in Varese, Italy.

A control group of healthy people will be required for further comparison of the findings. We will consider healthy people (both males and females; aged ≥18 years) without infection (negative for SARS-CoV-2), without symptoms of infectious diseases (neither chronic nor acute), and without chronic pathologies (N=30).

After the informed consent procedure, the sample will be divided into 4 subgroups according to the severity of clinical impairment, with at least 30 people in each subgroup. The severity of pneumonia cases will be measured with SMART-COP (systolic blood pressure, multilobar chest radiography involvement, albumin level, respiratory rate, tachycardia, confusion, oxygenation, and arterial pH) [30-32]. The following 4 categories of patients positive for SARS-CoV-2 infection will be analyzed: (1) asymptomatic patients (AS19); (2) mildly symptomatic patients with fever, tiredness, dry cough, diarrhea, etc and without full-blown pneumonia (PAU19); (3) patients with a diagnosis of pneumonia with a “low” risk score (SMART-COP) (POL19); and (4) patients with a diagnosis of pneumonia with a “moderate/high” risk score (SMART-COP) (ARD19).

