The 4- to 5-day monocyte culture will be further stimulated for 24 h with LPS (Sigma Aldrich) and IFNγ (Miltenyi Biotec) (M1 stimulus) or IL-4 (Miltenyi Biotec) (M2 stimulus) to investigate macrophage polarization, with assessment of surface M1 markers (TNFα and CXCL10 [BD]) or M2 markers (IL-10 and CCL18 [BD]) to check the prevalence of macrophage polarization in different groups of COVID-19 patients.

The epidemiological analysis will be carried out by integrating both vaccination history and the daily data collected after hospital admission. Azienda a tutela della salute Insubria archives will provide missing data.

Considering the immunological profile, patients with COVID-19 will undergo routine examinations and the following: lymphocyte immunophenotyping; determination of C3 and C4 complement fraction activity; determination of serum immunoglobulin (IgG, IgM, IgA, and IgE) levels; serum protein electrophoresis; determination of serum angiotensin converting enzyme levels [36,37]; cytomegalovirus serology tests; and determination of serum IL-6 levels.

A specific data collection form will store information quickly, and then, data will be collected in a database.

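### Signs, symptoms and biochemical findings are admitted without exclusion as candidate factors for severity, although some of them define the article's only severity groups

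*Protocol article*

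**What the plan says.** **Candidates.** The protocol article, Secondary Objectives, lists the material for identifying protective factors: earlier vaccinations, comorbidities, "clinical presentation of COVID-19 in terms of clinical signs and symptoms, and biochemical findings". It adds that recognising a population spared excessive inflammation "could define a risk score for the severity of COVID-19". Secondary Endpoints makes clear that the protective factors sought are those for severe COVID-19.

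**Severity.** Recruitment states that "the sample will be divided into 4 subgroups according to the severity of clinical impairment, with at least 30 people in each subgroup". The second group is "mildly symptomatic patients with fever, tiredness, dry cough, diarrhea, etc and without full-blown pneumonia (PAU19"); the first is asymptomatic. The third and fourth both have pneumonia and differ by SMART-COP band, the fourth being "patients with a diagnosis of pneumonia with a “moderate/high” risk score (SMART-COP) (ARD19"). The SMART-COP components are given as "systolic blood pressure, multilobar chest radiography involvement, albumin level, respiratory rate, tachycardia, confusion, oxygenation, and arterial pH". Sample Size carries the same four groups forward at 30 patients each.

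**Laboratory profile.** The end of the section on plasma and PBMC preparation lists the immunological tests, including "serum protein electrophoresis".

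No section says that an item used to form the groups is barred from the candidate list.

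**The concern.** The candidate list and the group definitions overlap. Symptoms, several clinical signs, and three laboratory or gas-exchange items (albumin, oxygenation, arterial pH) appear on both sides. An item that helps assign a patient to a group will differ between groups whether or not it has any bearing on the course of the disease, and none of the tests named in the statistical methods section can tell that difference from a real one.

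The objective is meant to inform treatment choice for the individual patient, and the Discussion speaks of tailoring therapies to a risk profile. A finding that, say, tachycardia or low albumin marks severe disease would partly restate how the patients were sorted. A score containing such items would look more discriminating than it is.

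**Working it through.** The plan gives no figure on this point, so there is none to reproduce. The check has two parts.

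**1. Candidates against group definitions**

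| Contrast | What separates the groups (Recruitment) | Overlap with the candidate list |
|---|---|---|
| AS19 vs PAU19 | presence of symptoms | symptoms |
| PAU19 vs POL19/ARD19 | diagnosis of pneumonia | pneumonia as part of clinical presentation |
| POL19 vs ARD19 | SMART-COP band | blood pressure, respiratory rate, tachycardia, confusion, radiograph, albumin, oxygenation, arterial pH |

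No overlap arises for vaccinations, comorbidities, lymphocyte immunophenotyping, complement, immunoglobulins, angiotensin converting enzyme, cytomegalovirus serology or IL-6. Serum protein electrophoresis matters only through an albumin fraction, if one is reported.

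**2. Size of the built-in association**

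Inputs from the article: 30 patients per group (Sample Size); two-tailed Mann-Whitney test and significance at P<.05 (statistical methods section).

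*AS19 vs PAU19.* Symptom presence is 0/30 vs 30/30 by definition, so AUC = 1.00. Fisher's exact two-sided p = 2 / C(60,30) = 2 / (1.18 × 10^17) = 1.7 × 10^-17. This is the definition restated, not a result.

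*POL19 vs ARD19.* The article gives no SMART-COP points or cut-offs, so these are assumed:
- eight mutually independent standard normal items, each flagged in 20%, 30% or 40% of patients;
- an unweighted count of flags, with the upper band starting at 2, 3 or 4 flags;
- 30 patients per band, 400 samples for each of the nine settings;
- AUC = U / (30 × 30) = U / 900.

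| Variable compared between bands | Mean AUC | Significant at .05 |
|---|---|---|
| Sum of the defining items | 1.00 | not tested: separation is by definition |
| One defining item | 0.62 to 0.67 | 35% to 63% |
| Marker outside the definition, unrelated to severity | 0.50 to 0.51 | 3.5% to 5.5% |

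The Monte Carlo standard error at 5% is √(0.05 × 0.95 / 400) = 1.1 percentage points, so the last row is compatible with the nominal level.

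A second simulation (1,500 samples per setting) took albumin as the item and set the upper band at a score of 3 or more. With equal weights, albumin differed by 0.47 to 0.48 SD and was significant in 45% to 49% of samples. With double weight on three other items, it differed by 0.29 to 0.34 SD and was significant in 19% to 28%.

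The exact percentage depends on the assumed weights, cut-off and prevalence. The excess over 5% appears in every setting.

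**The case against.** The strongest reply is that the article never commits to the circular analysis, and much of that reply stands.

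- **The score is tentative.** It is something that could be defined. No model, predictor set or outcome is fixed, and the four groups are not declared to be its outcome. A reader might infer that the score is to be built from group-defining variables; the text does not go that far.
- **Other sections point elsewhere.** Secondary Endpoints correlates clinical data and vaccination history with immune patterns, which is not circular, and names a contrast by outcome and ventilatory need. The Abstract's Conclusions and the Discussion describe the risk profile through vaccinations, comorbidities, immunophenotyping and cytomegalovirus status, without signs or symptoms.
- **Biochemistry as a whole is not compromised.** None of the listed immunological tests is named as a SMART-COP item. Albumin enters a second time only if electrophoresis reports it.
- **Two stronger readings fail.** One is that nothing is predicted because factor and label are both taken at enrolment. The article, however, uses daily data after admission and keeps patients in the study to discharge or death. The other is that defining items would crowd out vaccination and immune variables. That needs a multivariable model, and the article names only Pearson, Wilcoxon, Mann-Whitney and one-way ANOVA.
- **The rejection rates are illustrative**, since the scoring is assumed.

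These points narrow the concern without removing it. Identifying protective factors is a firm objective, the candidate list is stated without exclusion, and no other section withdraws it. Nor is this a detail left to an analysis plan: the list and the group definitions are both on the page, and they overlap.

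**Conclusion.** The concern holds in a conditional, item-specific form. If the four Recruitment groups serve as the severity outcome, the items that define the contrast in question are associated with it by construction, and that association cannot count as evidence of protection or risk. The groups are the only severity classification the article fixes, so this use is the natural one, though not the only one open.

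The separation is complete for symptom presence between AS19 and PAU19, and for the summed SMART-COP items between POL19 and ARD19; both follow from the definitions alone. For a single SMART-COP item the false-signal rate is well above 5% in every setting tried (19% to 63% across both simulations), but those values rest on assumed weights, cut-offs and prevalences and should not be quoted as properties of this trial.

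The point should be settled before the secondary analysis. It does not touch the vaccination, comorbidity and immune-marker comparisons.

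**What to change.** 1. In Secondary Objectives and Secondary Endpoints, state that for any comparison or score using the four groups as the severity outcome, the items defining the groups compared are descriptive only and not candidate factors: symptoms for AS19 vs PAU19; pneumonia for PAU19 vs POL19/ARD19; the SMART-COP components, with any albumin fraction from electrophoresis, for POL19 vs ARD19. The bar applies contrast by contrast. Fever or cough, for example, need not be barred between POL19 and ARD19, because neither is a SMART-COP component.
2. Alternatively, assess those items only against an outcome that arises after Day 0 and is already in the data set, such as death versus discharge (Participant Timeline). Ventilation should not be assumed available, because no section lists it as a recorded outcome.
3. Reconcile the candidate list in Secondary Objectives with the risk-profile lists in the Abstract's Conclusions and the Discussion, and with the contrast in Secondary Endpoints.

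**Cost.** The first and third changes are wording only. Results reports that the clinical data set is complete and the immunological analysis is still under way, so no new data are needed. Any score will show lower apparent discrimination. On the second route events may be few: 60 of the 120 patients (30 AS19 and 30 PAU19) are asymptomatic or mildly ill, and the article gives no number of deaths.

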#### Additional Objective

We were also interested in characterizing the phenotypes and state of the degree of activation of peripheral blood mononuclear cells (PBMCs), including monocytes, NK cells, and CD4^+^ and CD8^+^ T cells, in healthy subjects vaccinated with the Pfizer vaccine.

## Methods

### Trial Design

This will be an investigator-initiated, institution-led, nonpharmacological intervention for patients with COVID-19.

### Study Setting

The study will be conducted in “Ospedale di Circolo – ASST Sette Laghi,” a teaching hospital affiliated to the University of Insubria in Varese, Italy.

### Eligibility Criteria

The inclusion criteria will be checked before inclusion in the study. The inclusion criteria are as follows: age ≥18 years and documented SARS-CoV-2 infection, without sequencing to differentiate viral variants.

The exclusion criteria are as follows: refusal to the sign the agreement (informed consent); inability to sign the agreement; and HIV, hepatitis C virus, or hepatitis B virus (positive to hepatitis B surface antigen) infection.

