This epidemiological distribution of mortality rate remains unique, and it has not been noted in the successive pandemics of the 21st century [7]. A possible explanation for this is the advent of vaccines, with extensive vaccination after the 1930s. The population received vaccines 20 years before, and the Asiatic and Hong Kong pandemics showed the highest mortality rates after the fifth decade of life when the partially specific immunity had faded [7,8].

Additionally, transplant recipients and HIV-infected patients, characterized by a compromised immune system, unexpectedly do not seem to experience the worst complications of SARS-CoV-2 infection. An immune system imbalance could play a pivotal role during the viral infection, limiting destructive consequences of excessive inflammation.

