### Informed Consent

Inclusion will be feasible after patient approval, relative approval, or an emergency consent procedure (according to Italian law). The consent forms are available from the corresponding author on request. Day 0 will be considered the day of enrollment.

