### Outcomes

#### Primary Endpoint

The hypothesis is that monocytes, NK cells, and CD4^+^ and CD8^+^ T cells in patients with severe SARS-CoV-2 infection will show functional impairment. Moreover, innate cells will reveal overpowering hyperactivity, while adaptive T cells will show an impairment of activity that can provoke a pathologic inflammatory response with massive production of proinflammatory cytokines, edema, and pulmonary fibrosis.

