### Plans for the Collection, Laboratory Evaluation, and Storage of Biological Specimens

On day 0, blood samples (15 mL) will be drawn in EDTA tubes, centrifuged, and stored (−80°C) for subsequent analysis. After the first analysis, the remaining biological specimens will be kept for a maximum duration of 15 years.

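### Patients on immunosuppressive or immunomodulating drugs are eligible and the day-0 sample need not precede such treatment, so a drug effect can mimic or mask part of the immune pattern attributed to severe COVID-19

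*Protocol article*

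**What the plan says.** All references are to the protocol article.

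- **Eligibility Criteria.** Inclusion requires "age ≥18 years and documented SARS-CoV-2 infection, without sequencing to differentiate viral variants". Exclusions are refusal or inability to consent, and "HIV, hepatitis C virus, or hepatitis B virus (positive to hepatitis B surface antigen) infection". Both are given as complete lists. Neither mentions medication or transplantation.
- **Informed Consent.** "Day 0 will be considered the day of enrollment".
- **Plans for the Collection, Laboratory Evaluation, and Storage of Biological Specimens.** "On day 0, blood samples (15 mL) will be drawn in EDTA tubes". No section links the draw to the start of any treatment or sets a window from admission.
- **Recruitment.** "Patients will be recruited at the Emergency Department of" the study hospital. The 30 healthy controls must be free of chronic disease.
- **Primary Endpoint.** In severe disease, innate cells are expected to be hyperactive with massive cytokine production, while "adaptive T cells will show an impairment of activity that can provoke a pathologic inflammatory response".
- **Secondary Objectives.** The history data named are vaccinations, comorbidities, clinical presentation and biochemistry. Drug treatment is not named.
- **Statistical Methods.** Mann-Whitney tests, one-way ANOVA, Wilcoxon tests and Pearson correlations, with P<.05 as the threshold. No adjustment or stratification is named.
- **Background and Rationale.** The authors observe that "transplant recipients and HIV-infected patients, characterized by a compromised immune system, unexpectedly do not seem to experience the worst complications of SARS-CoV-2 infection".

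**The concern.** The readouts are T-cell IFNγ, monocyte and NK cytokine production, and plasma cytokines. Immunosuppressive and immunomodulating drugs act on these directly. Treatment started for the episode is plausibly more common in the pneumonia groups than in asymptomatic patients. The health requirement for controls largely screens out long-term exposure among them, but nothing does so among patients. Exposure can therefore differ along the same axis as the contrast of interest.

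A drug that lowers T-cell activity, used mainly in ARD19, would look like the predicted T-cell impairment. A drug that lowers cytokines would hide the predicted innate hyperactivity. The study intends to use these patterns to identify therapeutic targets and to support immunomodulatory treatment, so an artefact of treatment would feed into that inference.

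**Working it through.** **1. The plan's own figure.** The Sample Size section says that 30 per group can identify differences of 20% to 30%. It gives no SD and no power, so the figure cannot be reproduced. It can be bounded. At two-sided 0.05 the detectable standardised difference is (z₀.₉₇₅ + z_power) × √(2/30):

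- 80% power: (1.96 + 0.84) × 0.258 = 0.72 SD
- 90% power: (1.96 + 1.28) × 0.258 = 0.84 SD

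At 80% power, a 20% difference is detectable only if the coefficient of variation (CV) is at most 0.20/0.723 = 0.28, and a 30% difference only if it is at most 0.30/0.723 = 0.41. The 0.72 SD is the yardstick below.

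**2. Spurious difference on the SD scale.** Assumptions, none from the documents: no true disease effect, a treated patient's marker 1 SD lower, and untreated comparators. The spurious difference is the treated share of ARD19 × 1 SD. The last column is the simulated chance of P<.05 with the plan's Mann-Whitney test at 30 per group, where 5% would be correct.

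| Share of ARD19 treated | Spurious difference | Ratio to 0.72 SD | Chance of P<.05 |
|---|---|---|---|
| 20% | 0.2 SD | 0.28 | about 10% |
| 40% | 0.4 SD | 0.55 | about 28% |
| 60% | 0.6 SD | 0.83 | about 55% |

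**3. The same on the percentage scale.** Let f be the treated share in ARD19, f₀ the share in the comparator, and e the relative drug effect. The spurious difference is (f − f₀) × e. With 30 per group, normal approximation and f₀ = 0:

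| f | e | Spurious difference | P(significant), CV 0.3 | P(significant), CV 0.4 |
|---|---|---|---|---|
| 20% | 30% | 6% | 0.12 | 0.09 |
| 40% | 40% | 16% | 0.51 | 0.34 |
| 60% | 40% | 24% | 0.87 | 0.67 |

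Worked example, third row, CV 0.3. The ARD19 variance is 0.09 × (0.4 + 0.6 × 0.36) + 0.6 × 0.4 × 0.16 = 0.0938, and the comparator variance is 0.09. The standard error is √(0.1838/30) = 0.078, and 0.24/0.078 is about 3.07, giving a probability of 0.87.

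If 10% of the comparator is also treated, the third row becomes (0.6 − 0.1) × 0.40 = 20%, with probability 0.70 at CV 0.3.

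**4. Reading.** If few patients are treated before the draw, the effect is small. If treatment is common in ARD19, a drug effect alone can reach the 20% to 30% that the study is sized to detect.

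**5. Direction.** Exposure concentrated in ARD19 creates a difference in T-cell activity. Long-term immunosuppression among mildly ill patients shrinks the contrast between ARD19 and that group. Lower cytokine output in treated ARD19 patients works against the hyperactivity hypothesis. The sign of the net bias is not known in advance.

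**The case against.** The strongest reply is timing. Patients are recruited in the Emergency Department and bled on the day they enrol, so many samples should fall at or near presentation, before most in-hospital treatment. This stands as a real mitigation, and it makes the higher treated shares less likely. It secures nothing, however: no time limit is set, and it leaves long-term drugs and treatment begun before arrival untouched.

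Second, the sizes rest on assumed effects and shares. That is correct. They show a range, not an estimate.

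Third, a drug that lowers both T-cell activity and cytokines reproduces only half of the hypothesised pattern and opposes the other half. This also stands. A reader might infer that the severe-disease pattern will simply be a drug effect, and the documents do not support that.

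Fourth, a reader might see a contradiction between the Background, which pairs transplant recipients with HIV-infected patients, and the criteria, which exclude only the latter. There is none. HIV is listed beside hepatitis B and C, so the list reads as chronic viral infections. Keeping transplant recipients is defensible in an exploratory study that treats comorbidities as candidate protective factors.

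Finally, a sensitivity analysis or a medication record may exist in the full protocol or analysis plan, which are not shown. Their absence from the article is not the point. The point is that the article's stated criteria and sample timing leave the comparison exposed.

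**Conclusion.** The point holds in a limited form. As written, the criteria admit patients whose immune readouts are altered by drugs, the only research draw need not precede treatment, controls are selected to be largely unexposed, and the named comparisons are unadjusted. A drug effect can therefore be mistaken for, or can mask, part of the pattern attributed to severe COVID-19.

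The size cannot be read from the documents. Under the assumed 1 SD effect, 20% to 60% of ARD19 treated and untreated comparators, it is 0.2 to 0.6 SD, or 28% to 83% of the difference detectable at 80% power. Even the top of that range stays below 0.72 SD. With fewer treated patients, or with some comparators treated, it is smaller. It is worth addressing because the check is cheap and bears on what can be concluded about ARD19.

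**What to change.** Enrolment is complete, so eligibility can no longer change. The Results section reports the immunological analysis as ongoing, so the analysis still can.

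1. From the clinical records, flag each participant who has a transplant, or who received a systemic immunosuppressive or immunomodulating drug before the day-0 draw, whether long-term or started for this episode.
2. Report the number flagged in each severity group and in the controls.
3. Keep the all-participant severity comparison as the main analysis, and prespecify a sensitivity analysis in unflagged participants. Making the unflagged set primary is not advisable: it selects on a variable linked to severity and takes ARD19 below the planned 30.
4. If the two analyses differ, or too few unflagged ARD19 patients remain, state that the ARD19 pattern cannot be separated from treatment.

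The cost is a little record extraction and one added analysis. The sensitivity analysis will have a smaller and possibly milder ARD19 subset, so a loss of significance there must not by itself be read as a drug effect; compare the estimates and their intervals. Clinical management is unaffected.

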## Introduction

### Background and Rationale

Coronaviruses are common human and animal pathogens. During epidemics, they cause up to one-third of community-acquired upper respiratory tract infections in adults and probably play a role in severe respiratory infections in both children and adults. However, coronaviruses are responsible for a limited amount of diagnosed pneumonia and acute severe illness, especially in the younger population, and a coinfection is frequently detected in hospitalized patients. Usually, the infection is responsible for mild-to-moderate symptoms that rapidly and spontaneously resolve [1].

The new strain of coronavirus, SARS-CoV-2, belongs to the beta-coronavirus family, and it shares all community-acquired coronavirus transmission routes and symptoms. However, the transmission rate is significantly higher, with a faster viral spread responsible for the worldwide outbreak.

In fact, it is a novel virus that was most likely recently passed from bats to humans, and consequently, it is almost unknown to the human immune system. Besides, SARS-CoV-2 seems to undergo modification rapidly during its spread, further avoiding immune defenses [2].

A higher mortality rate characterizes the novel coronavirus, and it has reached over 3% [3]. The death rate is over 1% only for patients aged over 50 years, and it is under 0.4% until 40 years of age. No fatalities have been declared among children under 10 years of age. Furthermore, the death rate is almost double for males when compared with females [4].

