### Statistical Methods for the Primary and Secondary Outcomes

Associations between different variables will be examined using Pearson correlation coefficients. Paired comparisons will be made using the Wilcoxon matched pairs test. Nonpaired comparisons will be made using the 2-tailed Mann-Whitney test. Multiple comparisons will be made using appropriate one-way analysis of variance (ANOVA). A *P* value <.05 will be considered statistically significant. All statistical analyses will be performed using R version 3.4.3 (R Project for Statistical Computing) and SPSS 21 (SPSS Inc).

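### Acute co-infection is left out of the patient criteria, the severity groups and the stated comparisons, so innate hyperactivity in the pneumonia groups may partly reflect co-infection

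*Protocol article*

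**What the plan says.** All places are in the protocol article.

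- **Eligibility Criteria.** Patients enter on "age ≥18 years and documented SARS-CoV-2 infection, without sequencing to differentiate viral variants". Besides the consent criteria, the only exclusion is "HIV, hepatitis C virus, or hepatitis B virus (positive to hepatitis B surface antigen) infection". Nothing is said about acute bacterial or other respiratory viral infection.
- **Recruitment.** Controls must be negative for SARS-CoV-2, "without symptoms of infectious diseases (neither chronic nor acute), and without chronic pathologies". POL19 and ARD19 are formed from a diagnosis of pneumonia and the SMART-COP category. The cause of the pneumonia is not part of either definition.
- **Primary Objective and Primary Endpoint.** "Differences are expected among COVID-19 patients with varying disease severities and healthy people". The hypothesis for severe infection is that "innate cells will reveal overpowering hyperactivity, while adaptive T cells will show an impairment of activity".
- **Laboratory sections.** The readouts include IL-6, TNFα, monocyte markers and cytokine production after LPS stimulation. The one further infection named among the patient tests is cytomegalovirus, by serology, next to unspecified routine examinations.
- **Statistical Methods.** "Nonpaired comparisons will be made using the 2-tailed Mann-Whitney test". Several groups are compared by one-way ANOVA. No covariate is named.
- **Background and Rationale.** Of coronaviruses in general, the article says that "a coinfection is frequently detected in hospitalized patients".

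**The concern.** Co-infection can act on both sides of the main comparison. SMART-COP is built from signs such as respiratory rate, heart rate, oxygenation and multilobar involvement, none of them specific to SARS-CoV-2. A second infection of the lung can therefore move a patient into a higher severity group. The same infection can plausibly change circulating cytokines and monocyte activation. The article does not state that mechanism; it is a general immunological premise.

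If both links hold, a difference in innate activity between ARD19 and a milder group, or between patients and controls, can arise without any difference in the response to SARS-CoV-2. The article hopes to draw therapeutic targets and a risk profile from these patterns, so it matters whether a pattern is attributed to the virus or to a concurrent infection.

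**Working it through.** **1. The plan's own figure.** The article gives no figure on co-infection to reproduce. The group sizes agree: 4 × 30 = 120 patients, plus 30 controls = 150. Each pairwise comparison is therefore 30 versus 30, with P < .05 as the threshold.

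**2. Where co-infection could enter.**

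| Step | Patients | Controls |
|---|---|---|
| Eligibility | only HIV, HCV and HBsAg-positive HBV excluded | SARS-CoV-2 negative, no infectious symptoms, no chronic disease |
| Grouping | pneumonia plus SMART-COP, any cause | not applicable |
| Tests named | CMV serology, routine examinations | SARS-CoV-2 negative |
| Analysis | Mann-Whitney, one-way ANOVA, no covariate | same |

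No stated step separates a co-infected patient from one with SARS-CoV-2 alone.

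**3. Illustration of size.** The article supplies n = 30 per group, the two-tailed Mann-Whitney test and the .05 level. The following are assumptions: a share f of 10% to 30% of the pneumonia group is co-infected, nobody in the comparison group is, co-infection moves a marker by s = 1 to 2 SD in those patients, the marker is normal, and there is no SARS-CoV-2 effect at all.

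Only the co-infected patients move, so the group is a mixture:

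- mean shift = f × s, from 0.1 × 1 = 0.1 SD to 0.3 × 2 = 0.6 SD
- SD = √(1 + f(1 − f)s²), which at f = 0.3 and s = 2 is √(1 + 0.3 × 0.7 × 4) = √1.84 = 1.36

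Simulated share of trials with P < .05 (Mann-Whitney, 10,000 trials per cell):

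| Co-infected share | 1 SD shift | 2 SD shift |
|---|---|---|
| 0% | about 5% | about 5% |
| 10% | 6% | 8% |
| 20% | 11% | 20% |
| 30% | 18% | 38% |

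Separate simulations put the last cell between 38% and 40%. The range is therefore about 6% to 40%. A t-test on the same data reaches at most about 49%.

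**4. Both groups contain co-infected patients.** For ARD19 against POL19, a zero rate in the comparison group is not realistic. With 30% against 15% co-infected (assumed), the Mann-Whitney rejection rate is about 8% for a 1 SD shift and 13% for a 2 SD shift.

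**The case against.** The strongest case against has five parts.

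- **The background sentence is about something else.** It describes coronaviruses in general, before SARS-CoV-2 is introduced, and concerns hospitalized patients. This study recruits in the Emergency Department and draws blood on the day of enrollment, so infections acquired later in hospital matter less. This stands: the sentence shows that the issue was in view, but gives no rate for this population.
- **An article condenses the protocol.** Microbiology may be among the routine examinations, and a covariate may be specified in the full protocol or analysis plan. This stands in part. The point rests on the eligibility list, group definitions and tests that are stated, and does not claim that microbiology was not done.
- **The direction is uncertain.** On LPS-stimulated readouts, a prior bacterial exposure might lower the response. That is also an assumption, and it means co-infection could mask as well as mimic hyperactivity on those readouts.
- **The aim is exploratory.** The primary objective is descriptive, and unmeasured co-infection is a general limit of observational immunophenotyping. This argues for a sensitivity analysis, not for a change of design.
- **The remedy may itself be biased.** Sicker patients were probably tested more often, so dropping flagged patients could trim ARD19 selectively. This stands and shapes the fix.

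A reader might infer a much larger effect by treating co-infection as a uniform shift of up to 0.6 SD with unchanged spread, which gives a rejection rate of 62.8%. The assumptions do not support that figure: a shifted subset widens the spread, and the planned test is based on ranks.

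**Conclusion.** The point holds as a limit on attribution. Acute bacterial or other respiratory viral co-infection, beyond the excluded HIV, HCV and HBV and the serologically measured CMV, is neither excluded nor used in the group definitions or the stated comparisons, while controls must be free of infectious symptoms. Innate hyperactivity in POL19 and ARD19 may therefore partly reflect co-infection.

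The size is not known. Under the assumed rates and shifts, the chance of a false difference against an unaffected group rises from 5% to between 6% and 40%. At 10% co-infection with a 1 SD shift, it barely changes. Between two pneumonia groups that both contain co-infected patients it is lower.

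A reader might also infer that co-infection explains the expected hyperactivity, or that controls are proven free of every infection. The article supports neither. It gives no co-infection data in SARS-CoV-2, and controls are only required to be SARS-CoV-2 negative, free of infectious symptoms and free of chronic disease.

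**What to change.** 1. From microbiology already in the clinical record, code co-infection at day 0 for each patient as present, absent or not tested.
2. Report the numbers tested and positive in each severity group, so that uneven testing is visible.
3. Repeat the patient-versus-control and between-severity comparisons without flagged patients as a sensitivity analysis. For the comparisons between severity groups, the flag can instead be entered as a factor.
4. If the innate pattern does not persist, qualify its attribution to SARS-CoV-2. The repeat analysis should inform the wording of the conclusion and should not be a strict condition for reporting the pattern.

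This is still possible: the Results section says that enrollment and the clinical data set are complete and that immunological analysis is ongoing. No new patients or samples are needed. The cost is one variable, one repeat analysis and a slightly smaller sample in it. The main weakness is ascertainment, because sicker patients may have been tested more, and a patient who was not tested cannot be counted as free of co-infection. If no microbiology was recorded, state this as a limit on the conclusion.
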